## Discussion

This study has been designed to measure the effects of an augmented prescribed exercise programme for frail older hospitalised patients. The study design is based upon results of an earlier pilot study and issues reported from previously published studies. Therefore, this protocol differs from previous studies in three key areas: patient selection, intervention and outcome measurements.

Previous studies included some patients who were fully independently mobile but de Morton et al. [31] found that the intervention was most effective for those requiring an aid or assistance to walk. For this reason, we will exclude those who are independently mobile. For pragmatic reasons, we will also exclude those unable to walk at baseline, i.e., bed or chair bound.

There is strong evidence of low physical activity in hospital [32, 33] and Broderick et al. [34] found that many of the barriers could be addressed easily. For these reasons, we will not only deliver supervised exercise sessions, but in addition, will encourage mobility while in hospital and provide walking aids initially, if required. The exercises are designed to improve physical performance, transfer function, walking, balance and strength in order to maintain functional mobility as much as possible.

Our pilot study [13] showed that there was a considerable difference in physiotherapy contact time with the intervention, possibly introducing a Hawthorne effect. This has been addressed by using a sham intervention for the control group. To the authors’ knowledge, this is the first time that a sham intervention has been included in this type of study.

The intervention will be delivered by a senior physiotherapist. The interventions of previous studies have been delivered by a physiotherapist assistant or a physiotherapy student, under the guidance of a qualified physiotherapist [13,16,17]. However, patients’ physical performance fluctuates in the acute setting. If a qualified physiotherapist delivers the programme, it allows the optimal intervention to be delivered on a daily basis. It will also allow a greater opportunity to advise the patient regarding their independent physical activity in hospital and to address barriers to the intervention delivery such as pain relief.

Up to 27 % of the patients were unable to complete the Timed Up and Go Test in previous studies [16,17]. Therefore, the Short Physical Performance Battery will be used, which was found to be feasible and sensitive to change in a previous pilot study [13]. Length of stay will be used as the primary outcome measure as this is available electronically and absolutely complete data. A high attrition rate is predicted for the three-month follow-up attendance as our study group consist of frailer older adults.

A small number of studies have shown that interventions to increase older medical inpatients’ physical activity can be modestly beneficial. Previous authors discuss issues such as patient selection, intervention type and outcome measures. This protocol has been designed to include the frailer patient, to include a tailored and comprehensive intervention, and to measure the effects with the most valid outcome measure.

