## Methods

### Design and study size

The study is a single blind randomised controlled trial set in an acute 350-bedded teaching hospital. Power calculations based on the results of a pilot study indicated that a sample size of 200 (100 patients in each arm) would be required. To allow for an expected attrition rate of 5 % [18], two hundred and twenty medical patients aged 65 years and over are randomly allocated to either the intervention or sham arm in a ratio of 1:1. (see Fig. 1). The study has been approved by the Clinical Research Ethics Committee of the Cork Teaching Hospitals. (ECM 3 (vv) 13/10/15).

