#### Consent, assessment and exercise procedure

Upon screening, the medical team are contacted to confirm that there is no medical contra-indication to exercise for the patient. Eligible patients are informed of the study verbally and given a copy of the patient information leaflet. They give written informed consent to the study, including access to their medical notes, assessment at baseline, outcome and follow-up, and the twice daily exercise sessions. If the patient is considered to be cognitively impaired by the medical or nursing staff, the patients’ written consent is augmented by verbal assent from their next of kin. Patients with severe confusion, who are unable to follow commands, or are agitated, are not recruited to the study.

If recruited, patients are assessed (Time 1), and through concealed allocation, randomly allocated to the control group or the intervention group at that time. All recruited patients, who consent to wearing the accelerometer and with good skin condition at the ankle, are fitted with the SAM to measure physical activity in hospital.

For those in the intervention (Augmented Prescribed Exercise Programme, APEP) group, their exercise programme is prescribed to address their physical limitations identified through the assessment. The exercises are chosen to improve strength and balance, core stability, sit-to-stand function, balance (in standing and walking), walking and endurance. The intervention group are also actively encouraged to mobilise while in hospital, with assistance when necessary, and provided with walking aids initially, if required. The sham exercise sessions for the control group are not prescribed but consist of standardised stretching and relaxation exercises.

All exercise sessions begin within 24 h of group allocation and continue until the day before discharge. Verbal consent for each session is sought.

To ensure false step-count does not occur, the accelerometer (SAM) is turned upside-down (in this position, it is unable to record steps) when the patient is exercising at the bedside, i.e., not walking, and returned to the upright position before walking or at the end of the session.

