Patient compliance, exercise prescription and session duration is recorded. Within one day of planned discharge, all patients are re-assessed and the accelerometer (SAM) is removed from the patient by the RPT (Time 2; see Table 1). Patients who are deemed for long-term care (as they are unable to manage at home) or for end-of-life care are re-assessed on the date that the decision is made and those results are used.

The patients are reassessed at three months post discharge, by the RPT (Time 3, see Table 1). New onset of illness, physical performance, walking speed, quality of life and self-reported functional ability is measured. Hospital and Accident and Emergency utilisation since discharge is recorded.

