### Statistical analysis

The results will be analysed and presented as recommended by the CONSORT guidelines [30]. The primary outcome measure will be length of stay. This will be described using Kaplan-Meier “survival” curves and the results between groups will be compared using a log-rank test. Univariate and multivariate linear regression analysis will be used to determine differences in physical activity in hospital and physical performance, quality of life at discharge and three months post-discharge, and re-admission rates at three months.

This analysis will help to define whether a simple physiotherapy-led exercise intervention will shorten length of stay, increase physical activity in hospital, limit functional decline and readmission rates and improve quality of life in frail older hospitalised patients.

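### High three-month attrition is predicted, yet the only method named for three-month function and quality of life is linear regression, which as ordinarily fitted leaves discharge data unused and can understate the effect

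*Protocol article*

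**What the plan says.** All references are to the protocol article.

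- **Attrition.** The Discussion predicts: "A high attrition rate is predicted for the three-month follow-up attendance as our study group consist of frailer older adults". It gives no rate. The only attrition figure is in Design and study size: "To allow for an expected attrition rate of 5 % [18], two hundred and twenty medical patients", on a base of "a sample size of 200 (100 patients in each arm) would be required".
- **Analysis.** The Statistical analysis section says: "Univariate and multivariate linear regression analysis will be used to determine differences". The outcomes it lists include physical performance and "quality of life at discharge and three months post-discharge, and re-admission rates at three months". It names no other method for them.
- **Data available.** Table 1 (Measurements) schedules the SPPB (including walking speed) and the EQ-5D-5L at admission, at discharge and at three months. The procedure section places the discharge assessment within one day of planned discharge.
- **Health-care use.** In the account of the three-month reassessment, the procedure section adds: "Hospital and Accident and Emergency utilisation since discharge is recorded". It does not name the source. Consent is described as "including access to their medical notes, assessment at baseline, outcome and follow-up".
- **Primary outcome.** The Discussion chooses length of stay partly because it is held electronically and is complete.

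**The concern.** A linear regression of a three-month score on arm and baseline uses only patients who have that score. A non-attender contributes nothing, even though the same outcome was measured at discharge. Where high loss is expected, that wastes relevant data.

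The larger issue is selection. The intervention aims to improve strength, balance and walking by discharge. If patients with poor function at discharge attend less often, attendance depends on a variable that arises after randomisation and that treatment may alter. Low-functioning patients are then removed unequally from the two arms. Baseline covariates cannot correct this, because the selection acts on the change since baseline. What is at stake is the size of the three-month effect on physical performance and quality of life, which are secondary outcomes and the trial's evidence on lasting benefit.

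**Working it through.** **1. The plan's own figures.** The article gives no three-month attrition rate to reproduce. The 5% in Design and study size does not supply one: 200/0.95 = 211 and 200 × 1.05 = 210, while 220 randomised corresponds to 1 − 200/220 = 9.1%. The text does not say whether that allowance concerns the hospital stay or the follow-up. I therefore treat three-month loss as an assumption and use 15–40%, which leaves 220 × 0.85 = 187 down to 220 × 0.60 = 132 attenders.

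**2. When the arm difference is not biased.** On a standardised outcome (assumed baseline correlation 0.6, true effect 0.40 SD, attendance logistic in fitness with slope 1 per SD):

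- Loss driven by baseline fitness only: the regression on attenders gives 0.40 at every loss rate from 5% to 40%. Attenders' means are too high in both arms, but the difference is right.
- Loss driven by the three-month outcome itself: 0.39 at 5% loss, 0.36–0.37 at 20%, 0.34–0.36 at 30% and 0.35–0.37 at 40%.
- No true effect: the estimate stays near 0 in every case.

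**3. Loss that depends on discharge function.** Assumptions: 220 patients allocated 1:1; baseline SPPB mean 5, SD 2; residual SD 1.5 at each visit; a 1-point gain at discharge of which 0.75 remains at three months; attendance logistic in discharge SPPB; 1,500 replicates. Two estimators are compared:

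- *Attender regression:* three-month SPPB on arm and baseline, attenders only.
- *Likelihood estimate:* β(arm) + β(discharge) × δ. The two β come from regressing three-month SPPB on arm, baseline and discharge SPPB in attenders. δ is the baseline-adjusted arm difference at discharge in all patients. With complete discharge data this is what a repeated-measures model estimates.

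The true value is 0.75:

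| Loss | Log-odds slope per SPPB point | Attender regression | Attenuation |
|---|---|---|---|
| 25% | 0.3 | 0.74 | 0.01/0.75 = 1% |
| 25% | 0.5 | 0.71 | 0.04/0.75 = 5% |
| 25% | 0.8 | 0.64 | 0.11/0.75 = 15% |
| 25% | 1.2 | 0.62 | 0.13/0.75 = 17% |
| 40% | 0.3 | 0.72 | 0.03/0.75 = 4% |
| 40% | 0.5 | 0.68 | 0.07/0.75 = 9% |
| 40% | 0.8 | 0.63 | 0.12/0.75 = 16% |
| 40% | 1.2 | 0.58 | 0.17/0.75 = 23% |

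The likelihood estimate is 0.74–0.77 throughout. Its standard error is slightly smaller, for example 0.277 against 0.288 at 25% loss and slope 0.5. Simulation error in each mean is about 0.288/√1500 = 0.007.

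A separate set of runs over 15–40% loss gave 0.63–0.74 for the attender regression (16% down to 1% attenuation) and 0.75–0.76 for the likelihood estimate. There the likelihood estimate's standard error was equal or smaller even when loss was purely random. With no true effect, both estimators stay at 0.

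**The case against.** The strongest reply is that much of this is inference, and several parts of it stand.

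- **A reader might infer that the plan commits to separate complete-case regressions at each visit.** It does not say so. Analysis sets and missing-data methods are commonly left to a full protocol or analysis plan, and neither is shown. Their absence here is not a fault. What remains is that the article names a method, and that method in its ordinary form has this limitation under the loss the article itself predicts.
- **A reader might infer that the plan expects the frailer members of the cohort to be the ones lost.** The sentence explains a high overall rate by the frailty of the group. Loss that tracks discharge function is plausible, but it is an assumption.
- **The comparison need not be biased.** If loss follows baseline fitness, there is no bias in the difference. Baseline SPPB, SHARE-FI and CIRS-G are collected and could enter the multivariate model.
- **The bias is modest and conservative.** In a run with 25% loss the attender regression gave 0.67, so the bias is 0.75 − 0.67 = 0.08, about 0.08/0.284 = 0.3 of a standard error. In similar runs nominal 95% intervals still covered the truth 93–95% of the time. No false benefit arises.
- **A reader might infer that re-admissions will be under-counted among non-attenders.** The article does not make that record depend on attendance. Consent covers the medical notes, and the hospital holds electronic data, so records may already be the intended source. Under-counting is conjecture.

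The reply does not remove the case for change. The discharge measurements are already planned, and a model that uses them was no worse in any setting tried and closer to the truth in the setting of concern.

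**Conclusion.** The point holds in a limited form. The article predicts high three-month attrition and names only linear regression for the three-month functional and quality-of-life outcomes. As ordinarily fitted, that regression ignores non-attenders' discharge values. If attendance depends on discharge function, the estimated three-month difference can be attenuated by about 1–16%, reaching 23% only at the steepest slope tried with 40% loss. These sizes rest on an assumed loss rate, loss mechanism and set of SPPB variances, none of which the article gives.

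The stronger reading, that the planned comparison is biased, is not supported. The bias is conditional, runs towards no effect, and vanishes under the null or when loss depends on baseline alone. Length of stay is untouched. This is a worthwhile, low-cost improvement to key secondary analyses, to be settled before the data are analysed.

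**What to change.** Analyse SPPB, walking speed and EQ-5D-5L each with one mixed model for repeated measures: baseline value as covariate, discharge and three months as outcomes, and arm-by-visit terms. Every randomised patient with a discharge assessment then contributes, and the three-month contrast is read from the same model. Add a sensitivity analysis for deaths, for example scoring patients who died as 0 on the SPPB.

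Optionally, confirm that 90-day re-admission and death are taken from hospital records for all randomised patients under the existing consent, whether or not they attend. Keep patient report as a supplement, because one hospital's records miss admissions elsewhere.

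The cost is slightly more analysis and, if not already planned, a record look-up. No new visit or measurement is needed. The model relies on data being missing at random given baseline and discharge values. If attendance depends on the unseen three-month state beyond that, some bias remains, and the report should say so.

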## Abbreviations

6-CIT: Six-Item Cognitive Impairment Test
APEP: Augmented prescribed exercise programme
CIRS-G: Cumulative Illness Rating Scale – Geriatrics
EQ-5D-5 L: EuroQol 5-Domain 5-Level Scale
FES-I: Falls Efficacy Scale International
N-EADL: Nottingham Extended Activities of Daily Living Scale
PI: Principal Investigator
RA: Research Assistant
RPT: Research Physiotherapist
SAM: Stepwatch Activity Monitor
SHARE-FI: Survey of Health, Aging and Retirement in Europe Frailty Instrument
SPPB: Short Physical Performance Battery
